## Abstract

**Background:**

Acupuncture is a widely used complementary therapy; however, the central mechanisms underlying its effects, particularly how stimulation at different specific acupoints modulates brain function in distinct or common ways, remain poorly understood. This gap persists due to a lack of large-sample, systematic comparative studies under a unified experimental paradigm. Task-based and resting-state functional magnetic resonance imaging (fMRI) offer powerful tools to capture both the instant and sustained neural responses to acupuncture.

**Methods:**

We designed a randomized, single-blind, controlled trial. To achieve high statistical power and generalizability, 250 healthy participants will be enrolled. Each participant will undergo acupuncture at one of seven predefined acupoints (verum) and its corresponding non-acupoint (sham control) in two separate sessions, with a 1-week interval. Each session includes: (1) resting-state fMRI before and after needle manipulation, and (2) task-fMRI during the manipulation. The primary outcomes are fMRI-derived brain activity and functional connectivity patterns. Blinding assessment and the Modified Massachusetts General Hospital Acupuncture Sensation Scale-Chinese version (C-MMASS) will be collected to evaluate the credibility of sham control and the Deqi sensation.

**Discussion:**

This study is novel in its comprehensive approach to mapping the neural correlates of multiple acupoints within a single, rigorous design. We anticipate that our results will provide the first systematic characterization of the “acupoint-brain functional network” map, elucidating both common activation patterns across acupoints and acupoint-specific differential responses. This will significantly contribute to understanding the functional neuroanatomy of acupuncture and provide high-level evidence for its mechanism of action, ultimately helping to bridge the gap between traditional practice and modern neuroscience.

**Conclusion:**

The findings of this trial are expected to establish a robust empirical foundation for the neural basis of acupuncture, offering insights that could validate clinical practice and guide future target-specific acupuncture applications.

**Clinical trial registration:**

Identifier ITMCTR2025000066.

## Introduction

1

Acupuncture, an ancient Chinese therapeutic practice dating back over 2,000 years (1), is a non-pharmacological therapy rooted in Traditional Chinese Medicine (TCM) and its Meridian Theory. It is believed to regulate bodily functions by stimulating vital energy (Qi) at specific acupoints, which then travels along meridians to treat various diseases. According to a recent review, acupuncture shows therapeutic potential for more than 70 conditions, with moderate to substantial evidence supporting its efficacy in at least 8 specific diseases (2). Nonetheless, its underlying mechanisms—particularly how stimulating distal acupoints (remote from the affected area) elicits therapeutic effects through meridian pathways—remain unclear.

The focus of research on these mechanisms has undergone a paradigm shift, moving from the periphery to the central nervous system (CNS). There is growing consensus that the insertion and manipulation of acupuncture needles generate complex somatic afferent signals, which are integrated and processed within the brain (3, 4). This central neuromodulation is crucial not only for mediating analgesia—through the regulation of pain-processing regions like the anterior cingulate cortex and periaqueductal gray (5, 6)—but also for influencing higher-order cognitive and affective processes. Emerging evidence indicates that acupuncture can significantly modulate functions such as attention, emotion regulation, and interoceptive awareness by altering activity in key brain networks (7, 8).

The advancement of multi-modal neuroimaging has been instrumental in delineating these neural mechanisms, with each technique offering unique insights: functional magnetic resonance imaging (fMRI), with its high spatial resolution, excels at mapping the brain’s hemodynamic response and has been pivotal in demonstrating that acupuncture modulates functional connectivity within and between large-scale networks (e.g., DMN, SN, executive control network) in various patient populations (9, 10). Electroencephalography (EEG), providing millisecond-level temporal resolution, captures the dynamic electrophysiological brain responses to acupuncture, such as the normalization of aberrant EEG microstates in patients with post-stroke depression (11, 12). Structural MRI (sMRI) has revealed that sustained acupuncture intervention can induce neuroplastic changes, evidenced by alterations in gray matter density or white matter integrity in specific pathways (9). While these complementary approaches collectively affirm that acupuncture’s CNS effects are robust and reproducible, a direct comparison highlights a critical gap: fMRI is uniquely positioned to bridge the spatial specificity of acupoint effects with the network-level dynamics that underlie cognitive changes, making it the ideal modality for investigating how acupoint stimulation influences organized brain networks.

Despite this progress, the neuroimaging literature on acupuncture is fraught with methodological inconsistencies that obscure a clear interpretation. Many previous fMRI studies employ combinations of acupoints (13, 14), making it impossible to attribute observed effects to any single acupoint. Furthermore, studies focusing on individual acupoints are often hampered by small sample sizes (15, 16) and inadequate sham-controlled designs (16, 17), thereby conflating specific neuromodulatory effects with non-specific placebo responses.

To address these limitations, the present study employs a rigorous, single-acupoint design under a well-controlled, task-based fMRI paradigm. We focus on a therapeutically significant and commonly used acupoint to precisely investigate its distinct impact on functional brain network dynamics. Our objectives are twofold: (1) to isolate the specific central effects of a defined acupoint from non-specific responses using a robust sham-control design, and (2) to interpret these findings within the established framework of CNS network modulation, thereby contributing to a more precise understanding of acupuncture’s neural mechanisms and its potential applications in cognitive regulation.

## Methods

2

### Study design

2.1

This prospective, single-center, randomized, single-blind, placebo-controlled study will enroll 250 healthy participants. Participants will undergo acupuncture in separate sessions at one of seven predefined acupoints (verum acupuncture) and its corresponding non-acupoint (sham acupuncture), with a 1-week interval between sessions (18) (Figure 1). All participants will undergo two identical fMRI scanning sessions, separated by a 1-week interval, which corresponds to the washout period between the two acupuncture interventions. Each session will include resting-state fMRI scans before and after acupuncture, as well as task-based fMRI scans during acupuncture (Figure 2). The sequence of verum and sham protocols will be randomized across all fMRI runs, and the order of presentation will be counterbalanced across subjects (18).

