### Sample size

2.3

Currently, there are no standardized criteria for determining sample sizes in MRI studies, as they are often constrained by practical considerations such as scanning time and cost. Based on an efficiency analysis of sample size estimation in MRI research, a previous study indicated that approximately 12 participants are required to achieve 80% power at the single-voxel level for typical activation effects (19). In line with this reference and considering the study design, we set a sample size of 30 participants per acupuncture point. Each volunteer will undergo both verum and sham acupuncture at the same acupoint, resulting in a total of 210 experimental sessions. To account for potential data loss due to head motion or participant dropout, we plan to enroll a total of 250 subjects.

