### Randomization, allocation concealment, and blinding

2.4

In this study, participants will be randomly assigned to one of the seven acupoint groups. The randomization sequence is generated using SPSS 26.0 software, and the allocation scheme is concealed using opaque sealed envelopes. Upon participant enrollment, the allocation will be revealed by sequentially opening the envelopes to determine the assigned acupoint for acupuncture. The blinding procedure involves three aspects: first, participants are blinded to the specific acupoints used in the trial; they are only informed that the acupoints are located in the distal limbs. Second, radiologists, due to their professional constraints, are unaware of the specific acupoints and their significance, ensuring the objectivity of the scanning process. Third, image processors are blinded to the participants’ group assignments, ensuring the objectivity of the image processing.

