#### Blinding assessment

2.6.3

When recruiting and screening eligible participants, subjects will be informed that they will receive both verum and sham acupuncture stimulation while the orders of presentation remain blinded to them. Following the completion of two fMRI scanning sessions, participants will be asked to guess the type of acupuncture they received during each session to assess the blinding effectiveness. The question posed to participants will be: “Which type of acupuncture do you believe you received during the two sessions?” Participants will be provided with three response options: traditional acupuncture, sham acupuncture, or uncertain.

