Currently, there are two major paradigms for task-based fMRI study: non-repeated event-related (NRER) design and block design. NRER designs effectively capture transient neural responses to discrete stimuli (e.g., instantaneous needle insertion) (47). In contrast, our block design paradigm better reflects real-world clinical acupuncture practice which comprises four sequential phases: needle insertion, needle manipulations (lifting-thrusting and rotating) to elicit Deqi, needle retention and needle withdrawal. Acupuncture elicits prolonged neural and hemodynamic responses rather than transient bursts of activity. Block design, with its alternating periods of stimulation and rest (e.g., 60 s needle manipulation followed by 60 s rest), optimally captures these sustained effects. Furthermore, as the most commonly applied and the most efficient paradigm (46, 47), block design has the advantages of a relatively large blood oxygen level dependent (BOLD) signal change relative to baseline (48), superior signal-to-noise ratio (SNR) and increased statistical power (47, 49).

However, there are some limitations in this study. Firstly, due to resource constraints, this study will be unable to encompass all acupoints. Future work will be needed to construct a comprehensive brain mapping encompassing all acupoints to better inform clinical practice. Secondly, considering the characteristics of acupuncture, it is difficult to design a practitioner-blinded trial. Thirdly, the study will be limited to manual acupuncture, which may introduce variability due to subtle differences in needle manipulation techniques. Furthermore, different acupuncture modalities (e.g., electroacupuncture vs. manual acupuncture) may induce different effects (46, 50, 51). Future studies should compare outcomes across different acupuncture modalities to determine modality-specific neural correlates. Finally, although a sham acupuncture control will be employed, this approach may not eliminate the influence of placebo effects inherent in acupuncture trials.

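### Verum/sham session order lies outside the described envelope procedure, and the stated rule for it does not secure balance within each acupoint group

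*Protocol article*

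**What the plan says.** Two sections of the protocol article deal with random assignment, and they cover different things.

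- **Randomization, allocation concealment, and blinding.** Here "participants will be randomly assigned to one of the seven acupoint groups". The sequence is generated in SPSS, "the allocation scheme is concealed using opaque sealed envelopes", and at enrolment "the allocation will be revealed by sequentially opening the envelopes to determine the assigned acupoint for acupuncture". Session order is not mentioned.
- **Study design.** Each participant has one verum and one sham session a week apart. On order, the text says: "The sequence of verum and sham protocols will be randomized across all fMRI runs, and the order of presentation will be counterbalanced across subjects". It names no generation method, no concealment and no stratification by acupoint.

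Three other places bear on the point. Under Blinding assessment, "subjects will be informed that they will receive both verum and sham acupuncture stimulation while the orders of presentation remain blinded to them". The limitations in the Discussion concede that "considering the characteristics of acupuncture, it is difficult to design a practitioner-blinded trial". Under Sample size, "we set a sample size of 30 participants per acupuncture point".

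**The concern.** Each participant receives verum and sham at a single acupoint, so the verum-sham contrast is made within the person and within the acupoint group. Randomising the acupoint protects comparisons between acupoints. It does nothing for verum against sham; session order does that work. The generation and concealment steps that the article spells out are therefore attached to the other assignment.

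The order rule is also hard to apply as worded. Each session delivers one protocol, and its functional runs come in a fixed sequence (rest, task, rest). The only thing to randomise per participant is which session comes first, so there is nothing to randomise at the level of runs. Counterbalancing over subjects, unless it is done within acupoint, leaves the split in any one group of 30 to chance.

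A first scan may differ from a second through novelty, arousal or habituation. That session effect cancels from a paired mean only when order is balanced in the group being analysed. Otherwise each acupoint's map carries its own share of it, and the unequal shares can look like acupoint-specific responses, which the trial sets out to describe.

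**Working it through.** **Inputs from the article.** Seven acupoints with 30 participants each give 7 × 30 = 210; 250 are to be enrolled. The voxel-wise threshold for the task analysis is p < 0.005. No session effect is stated.

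**Assumptions.** Order is balanced 105/105 over the 210 but not within acupoint. The session effect π is taken as 0.25 to 0.5 SD of the within-person verum-sham difference. The contrast is an unadjusted paired mean.

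**Step 1: share of the session effect entering one acupoint's contrast.** A verum-first participant's difference contains +π and a sham-first participant's contains −π. With n1 and n2 participants in the two orders,

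shift in the mean = π × (n1 − n2)/n, so the share is |2p − 1| with p = n1/n.

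- 15:15 gives 0/30 = 0.
- 18:12 gives 6/30 = 0.20.
- 20:10 gives 10/30 = 0.33.

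**Step 2: how often such splits occur.** The number of verum-first participants in one acupoint is hypergeometric (30 drawn from 210, of whom 105 are verum first).

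| Split in groups of 30 | One given acupoint | At least one of seven |
|---|---|---|
| exactly 15:15 | 0.16 | – |
| 18:12 or worse | 0.32 | 0.91 |
| 20:10 or worse | 0.075 | 0.40 |

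The last column is from simulation with the overall balance held fixed. The mean share is 0.13, and the share in the worst of the seven acupoints averages 0.28. With independent coin-flips, 20:10 or worse has probability 0.0987 in one acupoint and 1 − (1 − 0.0987)^7 = 0.52 in at least one of seven.

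**Step 3: consequence at one voxel** (two-sided paired t-test, n = 30, no true verum-sham difference, before cluster correction).

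| Split | Shift, π = 0.25 to 0.5 | Type I error at 0.005 |
|---|---|---|
| 15:15 | 0 | 0.004 to 0.002 |
| 18:12 | 0.05 to 0.10 SD | about 0.005 |
| 20:10 | 0.08 to 0.17 SD | 0.008 to 0.014 |

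**Step 4: average over random orders.** Without conditioning on the split that occurred, type I error is about 0.004 at a nominal 0.005 and 0.046 to 0.048 at 0.05. The test keeps its level overall; the error sits in whichever acupoints happen to be unbalanced.

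**The case against.** The strongest reply is that this is a condensed article. How lists are generated, stratified and concealed is often left to the full protocol, which is not shown, and the flow chart is also unavailable. The article does say that order is randomised and hidden from participants. Counterbalancing across subjects is compatible with balancing inside each acupoint, and the remark about runs may simply mean sessions. A period term in the model, which an analysis plan could specify, would remove the effect of imbalance. Under random order the expected bias is zero, and any one acupoint reaches 20:10 or worse only 7.5% of the time.

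Much of this stands. It rules out three stronger readings that a reader might infer:

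- **That staff can choose the order.** The text says that order is randomised, and no passage gives anyone a choice. The remark about practitioner blinding concerns delivery of the needling, not who sets the order.
- **That balancing is done over the whole sample and nowhere else.** The text does not say so. The 40% is conditional on that case.
- **That the verum-sham maps are systematically biased.** Step 4 shows that they are not when order is truly random.

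What the reply does not remove is the mismatch between the two sections. The article does not leave allocation to another document. It describes the procedure and says that the envelope reveals the acupoint. The one sentence on order is worded for a different structure and, even on a generous reading, does not secure balance where the contrast is estimated.

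**Conclusion.** The point holds as a correctable weakness in how the order assignment is specified. The described concealment covers the acupoint, and the stated order rule neither fits two single-protocol sessions nor guarantees balance within acupoint.

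The size is modest and conditional. If balance is secured only over 210 participants, there is about a 40% chance that at least one acupoint's unadjusted contrast absorbs a third or more of the session effect. In SD terms, a 20:10 split means a shift of 0.08 to 0.17, but only under the assumed session effect of 0.25 to 0.5 SD. If the full protocol already balances order within acupoint, or the model includes a period term, the numerical consequence largely disappears and only the wording needs correction. The change is worth making because it costs nothing and protects the trial's central contrast.

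**What to change.** 1. **Randomization, allocation concealment, and blinding:** generate one list of 14 combinations (7 acupoints × 2 orders) in permuted blocks, and put both the acupoint and the order in the same opaque sealed envelope.
2. **Study design:** replace the order sentence with a statement that session order (verum first or sham first) is randomised 1:1 within each acupoint.

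The stated enrolment needs no change ("To account for potential data loss due to head motion or participant dropout, we plan to enroll a total of 250 subjects"). With blocks of 14, 250 = 17 × 14 + 12, so the last block is incomplete and the two orders differ by at most one participant in any acupoint at enrolment. Later losses may reopen a small gap.

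If randomisation has already begun, the article should state how order was actually assigned and concealed, and the two sections should be aligned with that. The cost is a regenerated list and two revised sentences, with no extra participants, visits or scans.

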**Figure 1 fig1:**
[figure not shown]
Flow chart.

**Figure 2 fig2:**
[figure not shown]
fMRI protocol.

### Participants

2.2

Participants in this study will be recruited from Shenzhen Traditional Chinese Medicine Hospital. Written informed consent will be obtained from each individual prior to enrollment.

#### Inclusion criteria

2.2.1

(1) Aged 18–45 years, regardless of gender.(2) Right-handed.(3) No clinically significant history of cardiovascular, respiratory, or neurological diseases.(4) No personal or familial history of psychiatric disorders.(5) No acupuncture treatment within the past month.(6) No fever or use of antipyretic analgesics within the past 3 months.(7) Willing to provide informed consent and sign the consent form.

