#### Exclusion criteria

2.2.2

(1) Pregnancy or lactation.(2) Individuals who do not respond to acupuncture stimulation.(3) Individuals with claustrophobia.(4) Those with metallic implants or other contraindications for MRI.

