#### Withdrawal criteria during the study

2.2.3

(1) Participants who fail to comply with the study procedures, thereby compromising data quality.(2) Those who experience severe adverse events or emergencies during the trial.(3) Participants unable to complete the study as scheduled.(4) Those exhibiting excessive head motion during MRI scanning, leading to unusable data.(5) Participants who receive other acupuncture treatments during the trial period.

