#### Verum acupuncture group

2.5.1

Following skin disinfection, an opaque, non-metallic sponge pad will be positioned on the skin surrounding the target area. Non-magnetic acupuncture needles (Suzhou Acupuncture & Moxibustion Appliance Co., Ltd., China; 0.25 × 40 mm) will be inserted to 2 cm deep into the designated acupoints on the right limbs (Table 1). After Deqi (A special sensation of acupuncture characterized by pain, soreness, distension, heaviness, or numbness), twisting (90–180°, 60–90 times/min), and lifting-thrusting (0.3–0.5 cm, 60–90 times/min) were performed for 1 min. During task-based fMRI scanning, the same twisting manipulation will be performed for 60 s at 60-s intervals (synchronized with scan initiation), continuing until completion of the 6-min 6-s protocol, followed by needle removal.

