#### Sham acupuncture group

2.5.2

Non-acupoints are localized at 1.5 cm lateral to the corresponding verum acupoints (Table 1), outside meridian trajectories and neurovascular bundles, avoiding tender points and hair follicles (Figure 3). Identical opaque, non-metallic sponge pads, as used in the verum group, will be placed on the skin surrounding the target area after disinfection. Blunt-tipped placebo needles (Suzhou Acupuncture & Moxibustion Appliance Co., Ltd., China; 0.25 × 30 mm) will be vertically placed on the skin surface without penetration, maintaining slight tactile pressure. Hence, the Deqi experience of the participants will not be overemphasized. Except locations of acupoints and needle penetration, the manipulation procedures and course will be the same with the verum acupuncture group (Figure 4).

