#### Demographic and basic clinical information collection

2.6.1

The demographic information (age, gender, education, marital status and occupation) and time of enrollment will be obtained at baseline.

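### A one-month acupuncture-free rule at a Traditional Chinese Medicine hospital leaves trained and experienced people eligible, which aggravates an existing weakness in participant blinding

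*Protocol article*

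**What the plan says.** On who may enter:

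- Section 2.2: "Participants in this study will be recruited from Shenzhen Traditional Chinese Medicine Hospital". It does not say whether these are staff, students, visitors or the general public.
- Section 2.2.1 has one rule on earlier acupuncture: "No acupuncture treatment within the past month".
- Section 2.2.2 has one exclusion that bears on acupuncture: "Individuals who do not respond to acupuncture stimulation". Training and past experience are not mentioned.
- Section 2.2.3 withdraws "Participants who receive other acupuncture treatments during the trial period", which concerns conduct after entry only.

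On blinding:

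- Section 2.4: "participants are blinded to the specific acupoints used in the trial; they are only informed that the acupoints are located in the distal limbs".
- Section 2.6.3: participants are told that they will have both real and sham stimulation, and only the order is hidden. They guess the type for each session after both are complete.
- Section 2.5.1: real needles "will be inserted to 2 cm deep into the designated acupoints on the right limbs" and are manipulated after Deqi.
- Section 2.5.2: sham needles "will be vertically placed on the skin surface without penetration, maintaining slight tactile pressure".
- Opaque pads are used in both conditions (sections 2.5.1 and 2.5.2), and participants are told to keep their eyes closed for scanning (section 2.6.2).

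On what is recorded, section 2.6.1: "The demographic information (age, gender, education, marital status and occupation) and time of enrollment will be obtained at baseline". Section 3.5 reads brain differences as more likely biological if the guesses do not differ significantly.

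**The concern.** A one-month window limits carry-over from recent treatment. It does nothing about familiarity. Someone last needled five weeks ago, or a clinician or student trained in acupuncture, meets every listed criterion, and the recruiting site is one where such people are plausible volunteers.

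Each participant compares two sessions, knowing that one is real. A person who remembers what a penetrating, manipulated needle feels like has a reference against which to label the sessions; a naive person has only the contrast between them. Once the session is labelled, expectation differs between verum and sham within that person, and it enters the contrast meant to separate specific from non-specific effects (the first objective in the Introduction). Section 3.5 uses the guesses to argue against that explanation, so it matters who is able to guess correctly and why.

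**Working it through.** **1. Reading the criteria together.** Take a TCM-trained adult, or a former acupuncture patient untreated for five weeks, who is otherwise healthy, right-handed and aged 18–45.

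| Section | Rule bearing on acupuncture | Keeps this person out? |
|---|---|---|
| 2.2.1 | none in the past month | no |
| 2.2.2 | non-responders excluded | no; if anything it favours people known to respond |
| 2.2.3 | no other acupuncture during the trial | no |

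Such people are eligible under the lists as written.

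**2. What remains hidden from them.** The pads and closed eyes hide the view. They do not hide penetration or Deqi, which are the differences between the two conditions that a person can feel. The order is unknown at the start, but the participant knows there is one session of each kind.

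**3. What the listed data would show.** Occupation is recorded and would flag many TCM staff and probably students. It would not identify lay people with past treatment, or how much they had had.

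**4. How far the guess question protects the interpretation.** The plan gives no figure to reproduce, so this is an illustration on assumptions that are not in the documents: a share e always recognises the real session, the rest guess 50/50, and the uncertain option is ignored.

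- Inputs: n = 30 per acupoint (section 2.3) and n = 7 × 30 = 210 pooled.
- Expected proportion correct: p = e × 1 + (1 − e) × 0.5 = 0.5 + 0.5e.
- Test: exact binomial against 0.5, upper tail at most 0.025. The critical count is 21 of 30 (tail 0.021) and 120 of 210 (tail 0.023).
- Detection probability: P(X ≥ critical count) with X binomial(n, p).

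| e | p | n = 30 | n = 210 |
|---|---|---|---|
| 10% | 0.55 | 7% | 29% |
| 20% | 0.60 | 18% | 82% |
| 30% | 0.65 | 36% | 99% |
| 50% | 0.75 | 80% | about 100% |

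Within one acupoint group, a non-significant guess comparison is weak evidence of intact blinding unless recognition is widespread. Pooled over all groups, detection is good from about 20% recognition upwards. Without an exposure variable, however, a positive pooled result would not show whether experience was the source.

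**5. Size of a naive-only analysis.** If a share s has had acupuncture, about 30 × (1 − s) remain per acupoint. For an assumed s of 20% to 60%, that is 30 × 0.8 = 24 down to 30 × 0.4 = 12 per acupoint, or 210 × 0.8 = 168 down to 210 × 0.4 = 84 pooled.

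**The case against.** The strongest reply is that experience is not the main route to unblinding. A needle inserted 2 cm and manipulated after Deqi, set against a blunt needle resting on the skin, can reveal the order to someone who has never had acupuncture, at the latest in the second session. This stands. Excluding trained people and looking at naive participants reduces one contribution and leaves the main one open.

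Other objections also stand:

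- The article names a recruiting site. It does not say that staff, students or acupuncture patients will be enrolled.
- The trial already collects guesses, makes its interpretation conditional on them, and concedes in the Discussion that sham may not remove placebo influence. That concession does not mention participants' experience.
- A journal article may leave case report form items and sensitivity analyses to documents not shown, so their absence is not itself a fault. The point rests on the eligibility lists that the article does state; recording and analysing exposure are companions to the change there.

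A reader might infer three stronger things that the documents do not support:

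- *That a trained person could tell the acupoint from the sham site 1.5 cm away.* The view is masked, and nothing in the article supports localisation that fine by touch.
- *That the data could show nothing of the effect.* Occupation would identify much of the trained subgroup.
- *That uneven experience across the seven groups biases the acupoint comparisons.* Assignment to acupoint is random, so such differences are ordinary chance imbalance, as for any personal trait. In the verum-sham contrast each person is their own control, so past exposure is the same in both sessions; it can modify the effect but cannot unbalance the conditions.

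**Conclusion.** The point holds as a modest, inexpensive improvement. As written, the criteria admit people with acupuncture or TCM training and people with past acupuncture experience. Such people are more likely to recognise the real session in a design where everyone knows that one session is real. This aggravates a blinding weakness that naive participants share.

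The size cannot be derived from the article: neither the share of such recruits nor their ability to recognise the sham is given. The detection probabilities rest on the stated guessing model. They show only that a non-significant guess result within one acupoint group is limited reassurance. They do not show that blinding will fail. Nor would it be right to conclude that the verum-sham contrast is invalid, or that restricting entry would secure the blinding.

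**What to change.** 1. In section 2.2.2, add an exclusion for people with acupuncture or TCM training (clinicians and students).
2. In section 2.6.1, record lifetime acupuncture exposure before the trial: never or ever, and approximate number of sessions. Occupation captures only part of this. If response to acupuncture is judged by test needling at screening, define naive status as of before that test.
3. In section 2.6.3, report the guesses by exposure as well as overall.
4. In section 2.7.3, repeat the verum-sham contrast in acupuncture-naive participants as a planned sensitivity analysis, pooled over acupoints where the per-acupoint numbers are small.
5. In section 3.5, state that experience is one contributor to unblinding and that naive participants may also recognise the real needle.

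The cost is one exclusion line, two questions on the case report form and one additional analysis. Some hospital staff and students can no longer volunteer, which may slow recruitment, and the naive-only analysis will be smaller and less precise than the main one. Exposure should be asked at enrolment, because it may be hard to recover reliably later.
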